#### Strategies to improve adherence to interventions {11c}

To promote engagement in the BEAM program, participants will be required to confirm availability for the Zoom telehealth sessions and complete the pre-test assessment (including the online survey and Zoom assessment) in order to be eligible for the study. Participants may opt out of the full Zoom assessment and complete a brief Zoom check-in instead if preferred. During the program, three scheduled weekly study-related notifications will be sent to participants in the intervention group through the BEAM app. Sending engagement reminders to participants has been found to contribute to greater mental health benefits from e-health interventions [53, 54] and increase the effectiveness of online parenting programs [55]. The proposed trial incorporates strategies such as reminders via email and telephone (SMS), which have also been shown to increase engagement [56]. Participants will receive a 1-page summary detailing the next steps in the BEAM program and will participate in a Zoom orientation meeting with a parent coach or clinical coach. The purpose of the orientation meetings is to welcome participants to the program, explain the program components, and answer questions, in an attempt to increase attendance and engagement in the program. Participants will be contacted by their clinical coach if they have not attended telehealth sessions for two weeks in a row. Parent coaches will also be assigned to facilitate and promote participant engagement on the forum.

#### Relevant concomitant care permitted or prohibited during the trial {11d}

Participants will be permitted to receive concomitant care for mental health problems, such as psychotherapy, medication, and/or support groups. No concomitant care and interventions are prohibited.

#### Provisions for post-trial care {30}

If further treatment is deemed necessary, a referral to another provider or clinic will be made, and a list of community services will be provided. No trial-related harms are expected.

### Outcomes {12}

#### Primary outcomes

The primary outcome is mean change in depression symptoms from pre- to post-intervention and from pre-intervention to follow-up, assessed using the Patient Health Questionnaire-9 (PHQ-9) [57], a self-report questionnaire that measures depression severity. Participant depression symptoms will be measured during eligibility screening pre-intervention (T1), immediately after intervention (T2), and at a 6-month follow-up (T3). The PHQ-9 includes nine items, asking participants to report over the past week how often they have been bothered by certain problems. Participants respond to each item using a 4-point Likert scale ranging from 0 (*not at all*) to 3 (*nearly every day*). Possible scores range from 0 to 27, with higher scores indicating more severe depression symptoms. Participant scores are summed, and a cutoff score of ≥ 10 will be used to identify participants who present with clinically concerning symptoms of depression [57]. The PHQ-9 cutoff score of 10 has been shown to demonstrate high sensitivity and specificity in detecting depression in a perinatal population [58].

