### Objectives {7}

The primary aim of this interventional study is to conduct an RCT to evaluate the efficacy of the BEAM app-based program for improving maternal mental health and parenting stress compared to a treatment as usual (TAU) control group. We hypothesize that participants who receive the BEAM intervention will report fewer depression symptoms (primary outcome) compared to the control group.

The secondary aims of the trial are to determine the benefits of BEAM for family relationships, parenting, and maternal and child socioemotional functioning. We hypothesize that participants who receive the BEAM intervention will report reduced anxiety symptoms, improved family relationship quality, more positive parenting skills, less parenting stress, and better child development outcomes. We will also explore whether changes in these outcomes occur as a function of treatment effects on maternal depression and parenting stress.

The current study will also examine exploratory outcomes of observed parent-child relationship quality, maternal sensitivity, and child emotion regulation via remote Zoom online assessments. Furthermore, exploratory outcomes will include physiological indices of wellbeing (e.g., sleep and daily activity) measured via Fitbits that participants will wear during the program. We hypothesize that participants who receive the BEAM intervention will display improved parent-child relationship quality, maternal sensitivity, and physiological health (e.g., improved sleep quality and increased daily activity) and that their children will demonstrate improved emotional regulation.

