#### Sample size {14}

Based on the findings from a meta-analysis, digital interventions for depression that include a human therapeutic guidance component (as is the case with the BEAM program group therapy sessions) have a moderate effect on depression (*g* = .63) [78]. Thus, an a priori, one-tailed, two-group power analysis was conducted using a moderate effect size (*d* = .5) using the G* Power 3 software [79]. The power analysis indicated that we would need 51 participants per group to reach 80% power (*α* = .05) to detect a clinically significant change in depression. To account for anticipated attrition of approximately 25%, a total sample of 140 with 70 in each group (intervention and control) will be the target for recruitment.

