## Statistical methods

### Statistical methods for primary and secondary outcomes {20a}

Between-group differences in primary and secondary outcome variables, as well as quantitative exploratory outcome variables (observational and Fitbit data), will be analyzed using linear mixed models. Models will test both a linear and quadratic time coefficient, where quadratic time coefficients will be removed from final models if not significant. An *α* of 0.05 will be used to determine statistical significance. Effect sizes of 0.20, 0.50, and 0.80 will be interpreted as indicating small, medium, and large effects, respectively [80]. Standardized effect sizes for linear mixed models will be derived based on existing recommendations for linear mixed models [80, 81]. The research team will also investigate if there is baseline moderation by symptom severity to examine whether the BEAM intervention is more effective than the control group for participants who have higher symptom levels at pre-intervention (e.g., depression, anxiety, insomnia).

Exploratory qualitative data will be analyzed thematically [82]. First, two analysts will concurrently, but independently read the transcripts for surface descriptive content, and organize like-with-like ideas. Second, transcripts will be re-read for latent meaning to better understand participants’ meaning, including looking for contradictory or confirmatory statements. Each analyst will independently generate and systematically apply themes across all transcripts. Semantic validity checks will ensure different words and phrases within a category have similar meanings [82]. To further enhance rigor, constructs will be deemed saturated (akin to statistical significance in quantitative work) when no new or additional constructs are identified, consensus is reached on all overarching themes, and no alternative explanations were found with subsequent interviews [82].

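### The primary outcome names two co-equal PHQ-9 comparisons at an alpha of 0.05, with no rule for which one decides, in a trial sized for one comparison

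*Protocol article*

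**What the plan says.** - Primary outcomes: "The primary outcome is mean change in depression symptoms from pre- to post-intervention and from pre-intervention to follow-up". The instrument is the PHQ-9, measured at pre-test (T1), post-test (T2) and follow-up (T3). Neither change is ranked above the other.
- Objectives {7}: the hypothesis is that "participants who receive the BEAM intervention will report fewer depression symptoms (primary outcome) compared to the control group". It singles out no visit.
- Statistical methods for primary and secondary outcomes {20a}: linear mixed models are used, an alpha "of 0.05 will be used to determine statistical significance", and "Models will test both a linear and quadratic time coefficient, where quadratic time coefficients will be removed from final models if not significant". The section gives no order, no division of alpha, no requirement that both changes succeed, and no sidedness. It does not say which coefficient or visit carries the primary claim.
- Sample size {14}: "an a priori, one-tailed, two-group power analysis was conducted", "using a moderate effect size (*d* = .5"; and "The power analysis indicated that we would need 51 participants per group to reach 80% power". This is one comparison, and no time point is attached to it.

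**The concern.** A confirmatory trial needs a rule, fixed in advance, that turns the primary data into success or failure. Here two comparisons carry the primary label, and each can be tested at 0.05. A report could rest its efficacy claim on whichever time point reached significance, and nothing in the article would rule that out. The overall error rate for the primary claim would then exceed 5%.

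The opposite reading, that both changes must be significant, protects the error rate but makes the trial weaker than its sample size implies.

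The mixed model does not settle the matter. With three visits, linear and quadratic time terms again offer more than one route to a group difference, and the final model depends on the data. Under Who will be blinded {17a}, the analysts know the allocation, so a rule fixed beforehand matters more than usual.

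**Working it through.** **Inputs.** From the article: two primary changes, alpha 0.05, d = 0.5, one-tailed sizing, 80% power, 51 per group, about 25% attrition, 140 in total, 1:1 allocation, no interim analyses. Assumed, because the article does not give it: the correlation ρ between the two test statistics, taken over a range.

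**1. The article's own figure.** Two-group t-test, one-sided 0.05: power = 1 − F(t₀.₉₅; df = 2n − 2, noncentrality d√(n/2)), with F the noncentral t distribution. At n = 51 the noncentrality is 0.5 × √25.5 = 2.52 and the power is 80.6%; 51 is the smallest n that reaches 80%. Attrition: 102/0.75 = 136, rounded up in the plan to 140; 140 × 0.75 = 105 completers, or 52.5 per group. The sample size is therefore right for one one-tailed test.

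**2. A plausible ρ.** With equal variances, two changes that share T1 have correlation (1 + r₂₃ − r₁₂ − r₁₃)/√[(2 − 2r₁₂)(2 − 2r₁₃)], where r is the correlation between visits. If all three are equal, this is (1 − r)/(2 − 2r) = 0.5. With r₁₂ = r₁₃ = 0.5 and r₂₃ = 0.7 it is 0.7; with 0.4, 0.4 and 0.8 it is 0.83.

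**3. If success at either time point counts.** Under no effect, with bivariate normal statistics:
- two-sided: 1 − P(|Z₁| < 1.96, |Z₂| < 1.96)
- one-sided 0.05: 1 − P(Z₁ < 1.645, Z₂ < 1.645)
- false benefit only, two-sided tests: 1 − P(Z₁ < 1.96, Z₂ < 1.96)

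| ρ | Two-sided | One-sided 0.05 | False benefit only (two-sided tests) |
|---|---|---|---|
| 0 | 9.75% | 9.75% | 4.9% |
| 0.3 | 9.5% | 9.3% | 4.8% |
| 0.5 | 9.1% | 8.8% | 4.5% |
| 0.7 | 8.4% | 8.0% | 4.2% |
| 0.8 | 7.8% | 7.5% | 3.9% |
| 0.9 | 7.0% | 6.8% | 3.5% |

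The last column compares with 2.5% for a single two-sided test.

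**4. If both must succeed.** The error rate cannot exceed 5%. Assume d = 0.5 at both visits and 51 per group, one-sided 0.05. Joint power is Φ₂(k, k; ρ), the bivariate normal distribution function, with k = Φ⁻¹(0.806) = 0.863. This gives 0.806² = 65% at ρ = 0, 70% at 0.5, 72% at 0.7 and 76% at 0.9.

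**5. Two remedies compared.** A fixed order keeps the error rate at 5% and leaves the first test its 80.6% power at 51 per group. Bonferroni (one-sided 0.025 each) needs 64 per group; 64/0.75 = 85.3, so 86 per group or 172 in total. With 52 completers per group, each Bonferroni test would have about 71% power.

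**The case against.** The strongest reply is that the article joins the two changes with an and, so both may be required, and then no error rate is inflated. That stands: the either-of-two rule is neither stated nor excluded, and a reader who infers that the trial has a 9% false-positive rate goes further than the text.

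Second, the stated analysis is a mixed model in time, not two change-score tests. If the quadratic terms are dropped, the group differences in both changes are multiples of one slope and collapse into one test. That also stands, so the table describes the case in which the two changes are tested separately. It does not rescue the plan: which case applies depends on the data, and no deciding coefficient is named in either.

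Third, an analysis plan that is not shown may set an order. It may, but the article itself fixes a two-part primary outcome and a single alpha.

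Three further inferences are tempting and not supported:
- That the sample size covers T2 in particular. Sample size {14} names no time point.
- That parenting stress could be promoted to primary. The aim does speak of "improving maternal mental health and parenting stress compared to a treatment as usual (TAU) control group", but the next sentence in Objectives {7} gives the primary label to depression alone, and the paragraph after it places parenting stress among the secondary hypotheses. The Abstract, Trial design {8}, Secondary outcomes and the assessment plan {18a} also treat it as secondary. The sentence is loosely worded, no more.
- That the secondary scales need adjustment now. That is commonly left to the analysis plan, and a familywise figure that treats scales answered by the same mothers as independent would mislead.

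**Conclusion.** The concern holds in conditional form. The article gives two primary comparisons equal rank, one alpha and no decision rule, while the trial is sized for one comparison.

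Read as either-of-two, the familywise error is about 7% to 9.75% for correlations from 0.9 down to 0. The figures at 0.5 (9.1% two-sided, 8.8% one-sided) rest on equal correlation among the three visits, which is an assumption. If the tests are two-sided, a false claim of benefit is about 4.5%, so how far this matters for an efficacy claim turns on a sidedness that the analysis section leaves open and the sample size sets as one-tailed.

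Read as both-required, there is no inflation, but the planned 80% power is not met short of almost perfect correlation. Each reading departs from the stated design: one on error rate, the other on power.

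**What to change.** Before analysis, name one group-by-visit PHQ-9 contrast from the mixed model as the single primary test, for example T1 to T2, the end of the intervention. Test the other contrast at the same alpha only if the first is significant. Keep the visit contrasts in the model whether or not the quadratic term is significant, so that the primary test does not depend on the data. State whether the tests are one-sided or two-sided. The sample size supports only a one-sided 0.05 test at 80%; a two-sided 0.05 test with 51 per group has about 71% power at d = 0.5.

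No extra participants or data are needed, and the first test loses no power. There are two costs. An effect seen only at the second-ranked time point could not support a confirmatory claim. The change is also an amendment that must go to the ethics board under section {25}, and the registered outcome should be checked against the new wording. Trial status reports that recruitment had finished and the intervention had started, so the choice should be dated and made without sight of outcomes by arm.

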#### Secondary outcomes

Secondary outcomes include mean change in maternal anxiety symptoms from pre- to post-intervention and from pre-intervention to follow-up assessed using the Generalized Anxiety Disorder 7-Item Scale (GAD-7) [59]. The GAD-7 is a self-administered scale with 7 items that are rated on a 4-point Likert scale (0 = *not at all* to 3 = *nearly every day*). A cutoff score of ≥ 10 will be used to identify participants who present with clinically concerning symptoms of anxiety. Scores range from 0 to 21, and participant scores are summed to obtain a total score. Higher scores indicate more severe GAD symptoms. The following suggested cutoff scores will be used: 10–14 (moderate anxiety) and 15 (severe anxiety). The mean change in parenting stress from pre- to post-intervention and from pre-intervention to follow-up will also be assessed using the Parenting Stress Index (PSI) [60], a self-report measure of parenting stress and interactional style. Scores are summed to obtain a total raw score ranging from 36 to 180, with higher scores indicating higher levels of parenting stress.

Additional secondary measures of parenting will be used to assess the mean change in family relationship quality across time points (T1 to T2 and T1 to T3). Parental assistance with child emotion regulation will be measured using the Parental Assistance with Child Emotion Regulation scale (PACER), a self-report measure of how parents use strategies to assist children with regulating their emotions [61]. Participant scores are summed to obtain a total score ranging from 50 to 350, with higher scores indicating greater engagement in strategies that support child emotion regulation. The mean change in parenting discipline practices will be assessed using the Parenting Scale, a self-report measure that assesses parenting behavior and dysfunctional discipline of in parents with young children [62]. Scores are summed to create a total score ranging from 30 to 210, with higher scores indicating higher levels of ineffective discipline practices. Parenting behaviors will be measured using the Parenting Young Children (PARYC) measure, a self-report of parenting strategies and behaviors of caregivers with young children [63]. Scores will be summer, and the mean change in scores from pre- to post-intervention and from pre- to follow-up will be assessed. Scores range from 21 to 105, with higher scores indicating more proactive parenting behaviors.

Other secondary measures include co-parent relationship quality and support, additional mother socioemotional functioning measures related to mental illness, and child outcomes. The mean change in all measures will be assessed from pre- to post-intervention and pre-intervention to follow-up. Change in partner support across time points will be measured using the Social Support Effectiveness Questionnaire (SSEQ), a self-report measure of partner support effectiveness [64]. Scores are summed to obtain a total score with possible scores ranging from 0 to 80. Higher scores reflect more effective social support. Change in romantic relationship satisfaction will be measured using the 4-item Couple Satisfaction Index (CSI-4) [65]. The CSI-4 measures global evaluations of romantic relationships. Scores range from 0 to 21 with higher scores indicating higher levels of satisfaction. Anger will be measured using the Patient-Reported Outcomes Measurement Information System (PROMIS) Short Form, a self-report measure of frequency and severity of anger [66]. The mean change in anger scores will be assessed between T1 and T2 and T1 and T3. Total scores range from 5 to 25 with higher scores indicating more anger. Change in self-compassion across time points will be assessed using the Self-Compassion Scale Short Form (SCS-SF), a self-report measure of self-compassion [67]. Scores range from 12 to 60 with higher scores indicating higher self-compassion. Self-esteem will also be measured with the Single Item Self-Esteem Scale (SISE), a single-item measure that assesses global self-esteem [68]. Scores range from 1 to 7 with higher scores indicating higher self-esteem. Sleep problems will be measured using the PROMIS Sleep Disturbance Scale, a self-report measure of sleep disturbance [69]. Scores range from 8 to 40 with higher scores indicative of greater severity of sleep disturbance. Change in suicidal ideation severity will be measured using the Depression Symptom Index Suicidality Subscale (DSI-SS), a 4-item self-report measure of suicidal ideation [70]. Scores are summed to obtain a total score with possible scores ranging from 0 to 12. Higher scores indicate higher suicide ideation. The change in substance use (alcohol and cannabis) will be assessed using the Alcohol Use Disorder Identification Test (AUDIT) [71] and Cannabis Use Identification Test - Revised (CUDIT-R) [72], respectively. The AUDIT is a self-report measure of alcohol consumption, drinking behaviors, and alcohol related problems with scores ranging from 0 to 40. Higher scores are indicative of more hazardous alcohol use. The CUDIT-R is a self-report measure of cannabis misuse. Scores on this measure range from 0 to 32, with higher scores indicating more hazardous cannabis use. Scores of 12 or more indicate a possible cannabis use disorder. The mean change in child emotional and behavioral problems will be measured using the Preschool Pediatric Symptom Checklist (PPSC), an 18-item parent report measure of emotional and behavioral problems in young children [73]. Item scores are summed to obtain a total score ranging from 0 to 34, with higher scores indicating higher incidences of emotional and behavioral problems. Finally, the mean change in child temperament will be assessed using a subset of questions from the Early Child Behavior Questionnaire (ECBQ), a parent measure of temperament in children aged 1 to 3 [74]. Scores range from 1 to 7 with higher scores indicating higher levels of the temperamental trait.

#### Exploratory outcomes

Exploratory outcomes include changes in parent-child relationship quality, sensitive parenting, and child emotional reactivity, using observational measures obtained during a remote Zoom video assessment with mothers and their children that will occur at pre- and post-intervention. Participants will also be asked to wear a Fitbit Inspire 2 throughout the trial. Various types of physiological data will be collected (i.e., heart rate, sleep quality and duration, and daily physical activity) at pre- and post-intervention in order to measure changes in heart rate, sleep duration, sleep quality, and physical activity. The Fitabase software will be used to manage data from participants’ Fitbits as Fitabase allows researchers to amalgamate data from across participant Fitbits [75]. The feasibility of the BEAM program will be assessed at post-intervention using the mHealth App Usability Questionnaire (MAUQ) [76] and other questionnaires developed for the BEAM program. Engagement and adherence linked to user IDs will be tracked from back-end app data using Firebase and Google Analytics, such as number of logins and time spent on the app, forum posts, and telehealth session attendance. A final exploratory outcome will involve analyzing the qualitative program data which will include the content of posts and comments within the forum and feedback from participants after the program completion (post-intervention) for program improvement purposes.

#### Descriptive measures

Descriptive data will be collected via survey questions on demographic and socioeconomic characteristics at pre-intervention. Items will include education level (high school degree or lower vs. post-secondary education), age, household income, changes in household income due to COVID-19, marital status (married or in a domestic partnership vs. other), number and ages of all children, type of community in which one lives (large city vs rural area), and medications. A measure of personality using the Big Five Inventory-10 (BFI-10), which will be adapted from the original questionnaire [77], will be administered at pre-intervention. Participants will also be asked about other treatments and service use throughout the duration of the BEAM intervention.

